#### Randomization

We used a computer program to randomize the three experimental groups and four fibromyalgia associations, taking into account the size of each center
[40]. The 449 participants were allocated to the three experimental groups as follows: CG = 154, IG = 153 and MIG = 142 (Table 
1). We applied another computer program to generate random sequences to select the participants from each fibromyalgia association for the experimental and control groups
[41]. The randomization results will be checked by analyzing potential confounders such as walking patterns, physical activity, impact of FM, pain, emotional status and age (see the “Statistical analysis” subsection below).

**Table 1 T1:** **Randomized experimental group-center assignments**^
**a**
^

**Patient associations**	**Assignment, **** *n * ****(%)**			**Total**
	**CG**	**IG**	**MIG**	
ADEFA	7 (28.0)	9 (36.0)	9 (36.0)	25 (100)
AFEFE	42 (39.6)	29 (27.4)	35 (33.0)	106 (100)
AFIBROM	73 (33.2)	87 (39.5)	60 (27.3)	220 (100)
AFIBROTAR	32 (32.7)	28 (28.6)	38 (38.8)	98 (100)
Total	154 (34.3)	153 (34.1)	142 (31.8)	449 (100)

^a^ADEFA: Fibromyalgia Association of Alicante; AFEFE: Fibromyalgia Association of Elche; AFIBROM: Fibromyalgia Association of Madrid; AFIBROTAR: Fibromyalgia Association of Talavera de la Reina (Toledo); CG: Control group; IG: Implementation intention group; MIG: Motivation and implementation intention group.

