#### Phase II (second and third years)

As our main outcome is a binary variable, backward stepwise logistic regression analysis will be applied. This method will allow us to investigate whether the experimental condition is associated with the acquisition of the walking pattern. Analysis will be performed for each time measure. Changes in walking behavior over time will be analyzed by applying a Cox proportional hazards regression model for recurrent events. Using this methodology, we will estimate the hazard function of the outcome measure (the likelihood of walking over time). We will analyze differences between groups by introducing the experimental condition as a predictor of the moment in the longitudinal study when women maintained the walking pattern.

Randomization results will be checked to ensure that groups are comparable at the beginning of the study in terms of their distribution of potential confounding factors (walking pattern, IPAQ, FIQ, pain, age, emotional status and behavioral intention). The potential confounders will be selected according to previous analyses at baseline by applying confusion criteria (associations with exposition: *P* ≤ 0.20 and correlation coefficients >0.10; associations with the main result in CG: OR < 0.67 or OR > 1.5). Statistical adjustment to control for the impact of confounders on effect estimation will be applied by introducing them into the analyses (if changes in OR are greater than 10%). Effect modifiers of basal walking pattern will also be tested.

Multiple regression analysis will be performed for each secondary outcome variable. Baseline data will be introduced in the predictive model for each time measure. We will test the mediating effects of the behavioral intention and of implementation intentions in the total sample using path analysis.

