It is important to underline that as soon as the final 274 participants agree to participate, strategies to avoid having participants dropping out will be implemented. In that sense, we will contact the 180 women who failed to attend the evaluation session but did not refuse to participate in the study. Because the participants belong to FM associations which conduct other activities for their members, we may have problems with the masking process. Participants might talk among themselves about the activities performed in each intervention group. However, nobody knows which intervention group is expected to be more successful. Participants will sign a commitment of confidentiality, and, furthermore, we will also assess the shaping of implementation intentions in the control group.

In spite of these limitations, the study addresses an important need: the enhancement of self-management in the treatment of FM. It focuses on increasing adherence to a strategy which has been shown to be effective (physical exercise, specifically walking). Furthermore, the results are expected to show the effectiveness of a short intervention which is easily applicable with a minimum of training and cost and that can be incorporated into routine clinical practice.

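### Women were allocated to arms within four patient associations, but association is not named among the phase II confounders or in any described phase II model; adding it is a nearly free improvement.

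*Protocol article*

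**What the plan says.** The Randomization section describes two steps. One program was used "to randomize the three experimental groups and four fibromyalgia associations, taking into account the size of each center"; a second was used to "generate random sequences to select the participants from each fibromyalgia association for the experimental and control groups". Table 1 gives the resulting counts by association and arm. The totals are stated in the text: "The 449 participants were allocated to the three experimental groups as follows: CG = 154, IG = 153 and MIG = 142".

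The same section says that the result will be checked on "potential confounders such as walking patterns, physical activity, impact of FM, pain, emotional status and age". The phase II part of the Statistical analysis section gives the list as "potential confounding factors (walking pattern, IPAQ, FIQ, pain, age, emotional status and behavioral intention", with numerical entry rules. A factor must be associated with exposure at P ≤ 0.20, and must also meet "correlation coefficients >0.10; associations with the main result in CG: OR < 0.67 or OR > 1.5". It is then kept if it changes the odds ratio by more than 10%.

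The phase II analyses are a backward stepwise logistic regression at each time point, a recurrent-event Cox model with experimental condition as predictor, a multiple regression for each secondary outcome with baseline data included, and a path analysis for mediation. None is described with association as a covariate or stratum. Association does appear in a phase I comparison, where age is examined by association, so the variable is on file.

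**The concern.** A factor used to structure allocation normally belongs in the analysis. It removes any between-site difference in outcome from the arm contrasts, and it matches the model to the way the arms were formed. Here the plan spells out its adjustment rule, with a list and thresholds, and the allocation factor is not on the list.

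The contrast most exposed is MIG against IG. It isolates the motivational component, and it is where the AFIBROM shares lie furthest apart. If walking success differed between associations, part of an unadjusted MIG-IG difference would reflect site mix. The document gives some reason to think that sites could differ. The associations run other activities for their members, the intervention is delivered in group sessions of at most 10, and distance from the study location hindered participation.

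**Working it through.** **Inputs.** Table 1 counts; planned increases of 10% (CG), 20% (IG) and 40% (MIG) from Sample size calculation; the entry thresholds from the phase II analysis section. The difference in success between associations is not in the document, so 10, 20 and 30 percentage points are assumed.

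**Step 1: reproduce Table 1.** The cell percentages and all row and column counts reproduce. The only discrepancy is the total-row MIG percentage, where 142/449 = 31.6% and the table prints 31.8; it has no bearing here. Re-expressed as the share of each arm that comes from each association:

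| Association | CG (154) | IG (153) | MIG (142) |
|---|---|---|---|
| ADEFA | 7 (4.5%) | 9 (5.9%) | 9 (6.3%) |
| AFEFE | 42 (27.3%) | 29 (19.0%) | 35 (24.6%) |
| AFIBROM | 73 (47.4%) | 87 (56.9%) | 60 (42.3%) |
| AFIBROTAR | 32 (20.8%) | 28 (18.3%) | 38 (26.8%) |

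**Step 2: is the imbalance more than chance?** The Pearson chi-square on the 4 x 3 table is 8.67, df 6, P = 0.19. Cramer's V = √(8.67 / (449 × 2)) = 0.098. IG against MIG across the four associations gives P = 0.084. The table is compatible with chance.

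**Step 3: what the plan's own screen would do.** If association were listed, P = 0.19 would meet the 0.20 criterion. A correlation of 0.098 (taking Cramer's V as the measure, which the plan does not specify) would fall just short of 0.10. Both are required, so adding association to the list would not by itself secure adjustment.

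**Step 4: how a site difference would carry into a contrast.** For arms A and B,

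shift = Σ over associations of (share in A − share in B) × success rate.

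If only AFIBROM differs, by d points, this reduces to (AFIBROM share in A − AFIBROM share in B) × d.

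| Contrast | Share difference | d = 10 | d = 20 | d = 30 | Planned difference (points) |
|---|---|---|---|---|---|
| MIG-IG | 0.423 − 0.569 = −0.146 | 1.5 | 2.9 | 4.4 | 20 (Sample size calculation) or 10 (Primary outcome measures) |
| IG-CG | 0.569 − 0.474 = 0.095 | 0.9 | 1.9 | 2.8 | 10 |
| MIG-CG | 0.423 − 0.474 = −0.051 | 0.5 | 1.0 | 1.5 | 30 |

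Shifts are absolute. If success is higher at AFIBROM, MIG-IG and MIG-CG are understated and IG-CG overstated; if lower, the reverse. AFIBROM against the rest is the worst two-level grouping for MIG-IG. For the other contrasts a different grouping is slightly worse: 1.1, 2.2 and 3.2 points for IG-CG (AFEFE and AFIBROTAR against the rest), and 0.8, 1.6 and 2.3 for MIG-CG (AFEFE and AFIBROM against the rest).

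**Step 5: effect on the test.** Simulation used 4,000 runs, 20% success at the other associations, no arm effect and a pooled z-test of MIG against IG. With the counts fixed at Table 1, the rejection rate is 5.8%, 7.9% and 11.4% for d = 10, 20 and 30. With arms redrawn at equal probability each time, it is 5.0%, 4.8% and 5.3%, with no average bias. The distortion is therefore conditional on the realised table.

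**The case against.** The strongest reply has four parts.

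First, this is a condensed article. The list in the Randomization section is introduced as examples, and the candidate terms of the stepwise model are not set out. Association may therefore enter through a fuller document. This stands in part: it rules out saying that a site imbalance could never be detected or adjusted for. It does not show that association enters any phase II analysis, and the phase II list is itself written as a complete bracket.

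Second, the evidence of imbalance is weak. A reader might collapse the table to AFIBROM against the rest and obtain P = 0.038 across three arms, or P = 0.012 for IG against MIG. That grouping is chosen after seeing the counts, and the full table gives P = 0.19. A reader might also infer that the chance of each arm was deliberately set differently by association. The text says only that centre size was taken into account, which does not establish this.

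Third, Table 1 describes 449 allocated women. All 582 eligible women were later contacted and 274 attended, with no split by arm and association. The analysed mix may be more or less even. This stands.

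Fourth, no difference in walking outcome between associations is documented. The remark "Because the participants belong to FM associations which conduct other activities for their members, we may have problems with the masking process" concerns masking and talk between arms, which an association term would not cure. The distribution of eligible and noneligible women, which depends largely on walking pattern, did not differ by association (P = 0.445). This also stands: the 10 to 30 points are illustrations. Adjustment for baseline walking pattern or intention might absorb part of any site difference, but only if those variables pass the screen.

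**Conclusion.** The point holds in a limited form. Allocation was within association, the realised arm mix differs between associations to a degree compatible with chance, and association is not named among the seven confounders or in any described phase II model. It does not follow that site differences do pass into the arm contrasts, or that the trial's estimates are biased. Over repeated equal-probability randomisation the unadjusted contrast is unbiased.

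What can be said is conditional on Table 1 and on an assumed additive AFIBROM difference of 10 to 30 points. The shift would then be 1.5 to 4.4 points for MIG-IG, 0.9 to 2.8 for IG-CG and 0.5 to 1.5 for MIG-CG. That is small against the planned 30 points for MIG-CG, and more noticeable where 10 points are expected. The actual size is unknown without outcomes by association and the mix among attendees. This is a cheap gain in robustness, not a threat to the trial's validity.

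**What to change.** In the phase II part of the Statistical analysis section, state that association is a fixed factor in the logistic and multiple regression models and a factor or stratum in the Cox model. Exempt it from the confounder screen and from backward elimination, since Step 3 shows that listing it alone might not retain it. Apply the 10% change-in-odds-ratio rule to models that already contain arm and association.

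ADEFA may be pooled with another association. It has 33 of the 582 eligible women; at the overall participation rate that is about 33 × 274/582 = 16 attendees (an assumption), or roughly five per arm, too few for a stable separate term at low success rates. Fix the pooling before outcomes are seen.

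The cost is wording and three degrees of freedom, or two with pooling. No new data are needed. With association in the model, the shift from an additive site effect is removed.

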### Description of the overall project

The study consists of two phases, both based on the same population.

Phase I, conducted over the course of 1 year, is a cross-sectional study with two measurement stages and the following three aims:

1. We will seek to gain access to the reference population, identify the eligible population, select the study population and identify the prevalence of our selected walking criteria (stage 1). The results of stage 1 are included in this paper.

2. We will seek to identify the predictors of the behavioral intention to carry out the selected walking program using the TPB and exploring the role of pain, impact of FM and fear of movement (stage 2).

3. We will seek to explore the concordance of walking behavior measurements (subjective and objective measures) (stage 2).

Phase II, which will be conducted over the course of 2 years, is an experimental, randomized, triple-blind study with two treatment groups and one active control group. Longitudinal measures will be taken at baseline and at 7 weeks, 3 months and 9 months of postexperimental intervention. One group will receive a motivational plus implementation intentions intervention (MIG), a second group will receive only an implementation intention intervention (IG) and the control group (CG) will be given a neutral task related to postural hygiene. The three groups will receive the same information on the benefits of physical exercise in FM. Motivational intervention will be based on the predictors of behavioral intention as measured and identified in phase I (stage 2) in order to create or strengthen the behavioral intention during the experimental study.

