This triple-blind study includes masking of the following groups in the manner described. Participants will know only that there are different intervention sessions but will not know the session contents; moreover, they will be unaware of the assumptions regarding the superiority of one intervention over another. Measures will be taken by researchers who do not participate in the treatment application and who are blinded to the experimental conditions. The statistician will also be blinded to the study protocol. The researchers who apply implementation intentions will also be blinded with respect to the MIG or IG experimental condition. In this phase, we aim to study the efficacy of the MIG intervention on unsupervised walking over the short term (7 weeks), medium term (3 months) and long term (9 months). The measurement at 7 weeks will be taken during the week after completion of the 6-week minimum walking program. We will base the selection of the medium- and long-term measurements on the assumption that the highest percentage of dropouts occurs between 3 and 6 months in supervised physical exercise programs
[8,9]. On the day of the intervention, a researcher will be responsible for the distribution of the participants into the three different treatment groups following random assignment. The researcher will remind participants of their confidentiality commitment.

Our main hypothesis is that a combined intervention (both motivational and volitional) will significantly increase walking behavior in comparison to the control group and that this effect will be higher than that in a merely volitional intervention in the short term and stable in the medium and long term.

Our selected walking pattern for FM patients is between two and four times weekly for about 50 minutes in bouts of 15 to 20 minutes, with a small rest between bouts to allow patients to avoid fatigue and continue the activity, for a minimum of six consecutive weeks

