#### Primary outcome measures

Two primary outcomes will be assessed as indicators of each intervention’s effect on exercise adherence:

1. We will measure the proportion of participants who perform the full minimum walking criteria (at least 30 minutes in bouts of 15 minutes with a small rest between bouts, twice times weekly over a minimum of 6 consecutive weeks) at the end of the 6-week period and the proportion of participants who have maintained it at 3 and 9 months. The expected efficacy of MIG is 30% higher than CG and 10% higher than IG.

2. Among participants who perform the full minimum walking criteria, we will focus on the proportion who reach the recommended pattern for FM patients at week 6 (between two and four times weekly for about 50 minutes in bouts of 15 to 20 minutes over a minimum of 6 consecutive weeks)
[31].

We will use the same self-reported measurements of the behavior from phase I (*ad hoc* self-reported items and daily logs) and pedometer readings.

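### The control-group-only confounder criterion conflicts, as written, with the claimed masking of the statistician, and it is a noisy selector.

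*Protocol article*

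**What the plan says.** Under Description of the overall project, the protocol article calls Phase II a "randomized, triple-blind study with two treatment groups and one active control group". It then lists who is masked, and the list includes the statistician: "The statistician will also be blinded to the study protocol".

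Under Statistical analysis, Phase II, the candidate confounders are "walking pattern, IPAQ, FIQ, pain, age, emotional status and behavioral intention". On how they are chosen, the text says: "The potential confounders will be selected according to previous analyses at baseline by applying confusion criteria". There are two selection criteria:

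- "associations with exposition: *P* ≤ 0.20 and correlation coefficients >0.10";
- "associations with the main result in CG: OR < 0.67 or OR > 1.5".

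The selected factors are then entered into the models "if changes in OR are greater than 10" per cent.

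Under Primary outcome measures, the main result is the proportion meeting the minimum walking criteria "at the end of the 6-week period and the proportion of participants who have maintained it at 3 and 9 months". It is therefore a post-baseline outcome.

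**The concern.** The second criterion is defined within one named arm and uses that arm's follow-up outcomes. Whoever applies it must know which arm is the control and must tabulate its results by covariate. This happens before the adjusted treatment odds ratio is fixed. An analyst who is masked to allocation cannot do this alone and stay masked to CG.

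The wording of the mask does not help. Read literally, a statistician kept from the protocol could not apply a protocol rule with fixed thresholds in a named arm. Read as masking to allocation, which is the sense of the list it stands in, it collides with the CG criterion.

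At stake is a design feature that the trial claims. The main hypothesis includes a comparison of the combined intervention with the control group, so knowing which arm is CG bears on a primary contrast.

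**Working it through.** **Which steps need CG identified**

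| Step in the Phase II analysis | Can it run on arms coded A/B/C? |
|---|---|
| Association with exposure (P ≤ 0.20, correlation > 0.10) | Yes |
| Association with the main result in CG (OR < 0.67 or > 1.5) | No: one code must be named as CG and its outcomes used |
| Adjust if the OR changes by more than 10% | Yes |
| Logistic regression at each time point | Yes |
| Cox model for recurrent events | Yes |

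Only one step needs the key. The text places the selection in analyses at baseline. Because the main result is measured at follow-up, that can only mean baseline covariates set against later outcomes.

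**How noisy the CG-only criterion is**

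The plan gives no figure here to reproduce. The inputs are:

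- 115 women per arm, from Sample size calculation.
- Rates of 10% (CG), 20% (IG) and 40% (MIG). That section gives these as expected increases from baseline. I take them as follow-up rates, since entrants do not meet the selected pattern at entry.
- Assumption: a binary baseline factor split 50/50, with no true association with the outcome.

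For such a factor, the information on the log OR in one arm is n·p·(1−p)/4, and SE = 1/√information. The thresholds on the log scale are ln 1.5 = 0.405 and ln 0.67 = −0.400.

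*CG only:*
- Information = 115 × 0.10 × 0.90 / 4 = 2.59, so SE = 0.622. About 11.5 events are expected.
- z = 0.405/0.622 = 0.652, upper tail 0.257.
- z = 0.400/0.622 = 0.644, lower tail 0.260.
- Chance of crossing either threshold: 0.257 + 0.260 = 0.517, about 52%.

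*Pooled over three arms, adjusted for arm:*
- Information = 115 × (0.09 + 0.16 + 0.24) / 4 = 14.09, so SE = 0.266.
- z = 0.405/0.266 = 1.52, upper tail 0.064.
- z = 0.400/0.266 = 1.50, lower tail 0.066.
- Chance of crossing: 0.130, about 13%.

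**Range**

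| Women per arm | CG rate | CG only | Pooled |
|---|---|---|---|
| 115 | 10% | 52% | 13% (IG 20%, MIG 40%) |
| 115 | 10% | 52% | 26% (all arms at 10%) |
| 115 | 20% | 39% | not computed |
| 91 | 10% | 56% | 18% (IG 20%, MIG 40%) |

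The 91 is 274/3. It assumes that the 274 women who attended the first evaluation divide equally among the arms.

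A simulation of the 115-per-arm case, with a Mantel-Haenszel odds ratio for the pooled version, gave 53% for CG only and 14% pooled. The normal approximation is therefore adequate.

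**The case against.** The case on the other side has several sound parts.

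- **Who runs the step.** The text is in the passive and does not assign the criterion to the masked statistician. Odds ratios could be produced in every coded arm, with a code holder reporting which set applies. A reader might infer that the blind is certain to be broken; the documents do not support that. An article may also leave code handling to a fuller document, so the missing procedure is not in itself the point. The point is that two statements which are present do not fit together.
- **How much is disclosed.** If CG were named, the two intervention arms could still be masked from each other. The masking of participants, assessors and the staff delivering implementation intentions would be untouched. A reader might infer that the triple-blind label as a whole is false; that goes too far.
- **Room for discretion.** The candidate factors and all thresholds are written down, so an analyst who knows CG has little freedom in this step. No route from that knowledge to a biased odds ratio has been shown.
- **How often.** Analysis at each time point is stated for the logistic model. The text does not say that confounder selection is repeated at every visit.
- **What 52% means.** It is chance crossing of one criterion. It does not measure unblinding, since a masked analyst would get the same figure. Nor is it the share of factors that end up in the model. If the exposure and outcome criteria must both be met, a null factor passes at most about 0.20 × 0.52 ≈ 10% of the time, before the correlation and 10% change filters.

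These points limit the size of the problem. They do not remove the conflict: the article describes staff masking in some detail, names no intermediary, and includes one step that cannot be run without the key.

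**Conclusion.** The point holds in limited form. As written, the CG-only outcome criterion conflicts with the stated masking of the statistician, because it alone requires the control arm to be identified, and its follow-up outcomes examined, before the adjusted effect is estimated. The phrase describing what the statistician is masked from is unworkable if taken literally.

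The criterion is also a poor selector. About 52% of null 50/50 factors cross it, against about 13% when the arms are pooled. These figures rest on 115 women per arm, follow-up rates of 10/20/40%, and a binary factor split evenly with no effect. The gap narrows if the intervention arms do no better than control (26% pooled). The figures describe this criterion alone, not the joint rule.

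**What to change.** Make two wording changes.

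1. In Statistical analysis, Phase II: assess the association between covariate and main result in the pooled sample, adjusted for coded arm (A/B/C), in place of the CG-only criterion. Every step can then run on codes.
2. In Description of the overall project: replace the statement on the statistician with one saying that the statistician works with coded arms and is blinded to the key linking codes to MIG, IG and CG until the covariate set and models are locked. The key is what must be withheld; the analyst needs the codes themselves to adjust for arm.

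Neither change needs new data, and the pooled criterion uses about three times as many women. Two limits remain. Covariate selection still depends on follow-up outcomes and on the 10% change step, so it stays data-driven. If the groups differ as expected, the coded results may suggest which one is CG.
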